**Proposed alternate approaches**

- a pneumonia score, with 10- 20 questions relating to signs and symptoms of pneumonia (see Annex – final version to be informed by local pilot).
- a video to demonstrate a child with signs and symptoms of pneumonia or of “cough or cold” to aid the accurate recall of the caregiver.
- pictures of locally available drugs/injections/syrups to aid the caregiver’s accurate recall of the treatment their child received.

**Study Outline**

Selection of Study Sites

Two sites have been selected: one urban site in Pakistan and one rural site in Bangladesh. Criteria for site selection included: 1) high rates of childhood pneumonia; 2) feasibility for mounting the study within a short time and at a high level of quality, based on past performance of the PI, capacity of the study team and reviews of facility records; and 3) cost (since funds to support this activity are limited).

A third site in sub-Saharan Africa would be highly desirable, and initial contacts have been made. Decisions about the Africa site will be made over the coming months based on whether a suitable site can be identified and the availability of project funds. In the meantime, the study will move forward in the two existing sites.

Characteristics of the sites are summarized in table 1.

**Table 1: Characteristics of the study sites**

| **Pakistan Urban** |  |
| --- | --- |
| *Geographic Location:* | Islamabad |
| *Principal Investigator:* | [name] |
| *Subcontracting Institution:* | Children’s Hospital, Pakistan Institute of Medical Sciences, Islamabad, Pakistan. |
| *Strategy for recruitment of children with pneumonia:* | Pneumonia cases identified at PIMS, a major children’s hospital by a trained doctor |
|  |  |
| **Bangladesh Rural** |  |
| *Geographic Location:* | Four rural villages: Mirzapur, Gorai, Bhatgram, Jamurki |
| *Principal Investigator:* | [name] [name] |
| *Subcontracting Institution:* | ICDDR,B |
| *Strategy for recruitment of children with pneumonia:* | Pneumonia cases identified at local government health services by a trained doctor |

*Recruitment at clinic*

Children aged 0 to 5 years who present to a health clinic or hospital out-patient department suffering from acute respiratory symptoms will be eligible to be recruited into the study. The children will be assessed according to a standard protocol by a study doctor and key clinical and treatment details recorded. A diagnosis of pneumonia, severe pneumonia or of “cough or cold” (no pneumonia) following an agreed clinical classification system and details of all treatment prescribed will be carefully recorded. Children presenting primarily with an episode of recurrent wheeze (reactive airways disorder / asthma) or who have pneumonia severe enough to require hospital admission or who have symptoms of more than 4 weeks duration or who have already received treatment from health services for the current illness episode will be excluded (so as to limit recall bias associated with the admission).

A detailed address will be recorded and consent sought for a follow up visit. The study will aim to recruit and follow up successfully 300 children with pneumonia (or severe pneumonia if this is treated in the community) and 300 with “cough or cold” (no pneumonia) at each study site. An attempt will be made to recruit all children with pneumonia who present during the defined study period when a trained clinical researcher is available. Children with “cough or cold / no pneumonia” will be frequency matched to pneumonia cases so that in any one week the age and sex distribution of cases of pneumonia and “cough or cold” are similar.

All children will then be treated according to the standard management protocols of that particular clinic. It is expected that some of the study children with pneumonia will go on to develop severe pneumonia, and require hospital referral. If this should happen the local health worker will ensure that the child is referred to the nearest health facility to receive medical care. A detailed record of the treatment given to the caregiver will be recorded.

It is recognized that children attending a clinic with pneumonia could represent a biased group that are not fully representative of all sick children. We will collect DHS data on socio-economic status in order to compare the sample population to a wider population. Furthermore, it is possible that the consent process and information sheet may introduce a source of bias in the recording of recall of symptoms and events.

*Follow up at home*

The primary caregivers of these children will first be interviewed using the DHS and MICS questions relating to pneumonia (see Annex) either at 2 weeks (200 with pneumonia and 200 with cough or cold) or 4 weeks (100 with pneumonia and 100 with cough or cold) after diagnosis. This will follow the DHS and MICS procedures as closely as possible. The order of administering the DHS and MICS questionnaires will be alternated with each child so that each is administered first on 50% of occasions. After this is completed they will then also be questioned about specific signs of pneumonia (which will form a pneumonia score - see below) and will be asked to watch a video of a child suffering from pneumonia and of a child suffering from an upper respiratory infection (asking which best represents their child’ respiratory illness episode). Finally, a drug chart will then be used to show them pictures of locally used medicines with a request to identify which medicines, if any, their child was prescribed. These research workers should be given the address details of the child but not be made aware of the study group of the child nor have access to the clinical details of the child recorded at recruitment.

*Home visit interview sequence:* The research worker will

1. introduce him/herself to the caregiver, and check that the details match those on the recruitment form.
2. inform the mother of the interview process and ensure that she is willing to participate (and obtain written consent).
3. check that the child’s details are correct, and make sure that the caregiver understands that the interview only concerns this child, and that she should only answer the questions in relation to this child.
4. start by asking the DHS questions (Annex 1) then ask MICS questions (Annex 2) – this sequence will be alternated from child to child to that DHS is asked first in 50% of children
5. ask pneumonia score questions (Annex 3)
6. show the caregiver the video clips and ask mother to identify which disease best represents her child
7. show the caregiver a drugs chart and ask her to identify with what her child was treated; note whether treatment information is based on this or actual observation of medications in the home
8. ask if the mother has a pharmacist’s note or a ‘road to health’ card, and record any information from the past 2 or 4 weeks.

*Study analysis*

The study report will include a detailed description of the epidemiological and health services characteristics of the study population

There will be 4 separate groups interviewed in this study:

- Mother’s whose child has been accurately diagnosed as having pneumonia (or severe pneumonia if this is treated in the community) by a physician, and is interviewed after 2 weeks.
- Mother’s whose child has been accurately diagnosed as having pneumonia (or severe pneumonia if this is treated in the community) by a physician, and is interviewed after 4 weeks.
- Mother’s whose child has been accurately diagnosed as not having pneumonia by a physician, and is interviewed after 2 weeks
- Mother’s whose child has been accurately diagnosed as not having pneumonia by a physician, and is interviewed after 4 weeks

Data from the interviews and the clinical case study forms will be used to calculate sensitivities and specificities of each of the above methods (DHS / MICS defined pneumonia; pneumonia defined by various pneumonia score thresholds; video-assisted recognition of pneumonia) for the diagnosis of pneumonia and for antibiotic treatment. These will be estimated for all possible pneumonia score thresholds so that an optimum performance threshold can be defined for the score. The caregiver will then be asked to show the research worker any pharmacist’s note, ‘road to health’ card or other health record which may have details of the illness and treatment given.

*Sensitivity + specificity calculations:*

|  | | **Medical diagnosis of Pneumonia** | | |
| --- | --- | --- | --- | --- |
|  | | **+ve** | **-ve** | **Total** |
| **diagnosis of “suspected pneumonia”**  **from DHS*** | **+ve** | **a** | **B** | **a+b** |
| **-ve** | **c** | **D** | **c+d** |
| **Total** | **a+c** | **b+d** | **n** |

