An experienced senior researcher will visit each study site before and once during the study period to ensure study procedures are being followed closely and in a similar fashion at each site. Training of clinic doctors and research worker s who conduct the follow up will cover

- Diagnosis of pneumonia
- Preparation of local pneumonia score and videos
- Study record forms
- MICS or DHS survey procedures
- Pilot study using the study procedures to recruit and follow up children to check that there are no major flaws in the planning or structure of the study and to address any problems which arise (this should include at least 5 children with pneumonia and 5 with “cough or cold”.
- Technical issues related to the video / PCs

This study forms will only be finalised after the training and pilot period and with the active participation of [name], WHO.

Plan of Analysis

The data sets will be used to describe the sensitivity and specificity of reported signs of suspected pneumonia for “proven pneumonia” (a pneumonia score system will give a range of sensitivities and specificities for each score – which will enable a cut off score to be selected with the best sensitivity and specificity) for the current DHS protocol and for alternative protocols using the combinations of the three strategies described above. In addition, the study team will compare the results obtained using two- and four-week recall periods.

Project outcomes:

- Sensitivity + specificity of interview based diagnosis of pneumonia with existing DHS / MICS survey methods; pneumonia score and video-assisted recall.
- Sensitivity + specificity of mothers recall of treatments with existing DHS / MICS survey methods and new pictorial approaches

Comparison of results from 2 weeks and 4 weeks recall period (including a comparison of recalled timing of delay in careseeking at these different time points).

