During the interview, the research worker will show the caregiver a chart which will contain pictures of all the locally used medications. The research worker will ask the caregiver which, if any, of these treatments her child received. This drug chart should be presented both as a separate laminated sheet and loaded onto the study laptop PC to be displayed after the video is shown. The drugs shown should be clearly displayed, with any identifying marks (e.g. markings) easily visible. The caregiver will also be asked about details of dose and duration of treatment given and source of the medication. The pilot study will consider methods proposed in the WHO manual edited by Hardon before the final study protocol is established.

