**Annex 5:** **Home follow up form**

Child’s Name (full): ………………………………………........................................

Age: …………………………………………………………………………………...

D.O.B: ………………………………………………………………………………...

Mother’s/

primary caregiver’s name: ………………………………………………......................

Address: ……………………..................

……………………..................

……………………..................

……………………..................

……………………..................

Date interviewed:………………………………………………………………...

DHS / MICS questions – TO BE ADDED

Pneumonia score – TO BE ADDED

Video exercise findings – TO BE ADDED

Treatment received – TO BE ADDED

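### Step 7 of the home visit does not require the drug-chart answer to be recorded before, and separately from, medicines seen in the home, so chart accuracy may mix recall with label reading

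*Protocol*

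**What the plan says.** The accuracy of treatment recall with a picture board of medicines is one of the Protocol's research questions. The project outcomes, under Plan of Analysis, list it as "Sensitivity + specificity of mothers recall of treatments with existing DHS / MICS survey methods and new pictorial approaches".

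The home visit interview sequence collects treatment information at three points:

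- Step 4, the survey questionnaires: "start by asking the DHS questions (Annex 1) then ask MICS questions (Annex 2"), with the order alternated from child to child. These include the survey questions on drugs taken.
- Step 7, the chart: "show the caregiver a drugs chart and ask her to identify with what her child was treated". The same step then adds "note whether treatment information is based on this or actual observation of medications in the home".
- Step 8, written records: the interviewer asks for a pharmacist's note or health card and is to "record any information from the past 2 or 4 weeks".

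Two other places describe the chart without mentioning medicines in the home. The follow-up text says "a drug chart will then be used to show them pictures of locally used medicines", and the Drug Chart note says "The research worker will ask the caregiver which, if any, of these treatments her child received". The home form in Annex 5 has one line on the subject: "Treatment received – TO BE ADDED". The treatment table under Study analysis sets what the mother said against what the child received, drug by drug. It does not say whether an answer read from a pack counts as something the mother said.

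**The concern.** Step 7 most naturally reads as one body of treatment information with a note of its source. Survey recall and written records each have their own step. Only chart recall and observed medicines share one, with no order fixed and no separate field required.

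An interviewer who follows the step as written may let the caregiver fetch the medicines and then record what the label shows. If such an answer enters the chart table, the chart is credited with reading a label. Step 4 describes no such route, so the contrast between the chart and DHS/MICS becomes unequal. If such answers are left out, the homes removed are a selected group. The source note identifies these children but cannot restore an unaided chart answer that was never written down.

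The comparison of recall periods is exposed in the same way if medicines are still in the home more often at 2 weeks than at 4 weeks. A difference in pack availability could then look like a difference in memory.

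**Working it through.** The Protocol states no figure for this point, so there is nothing to reproduce. The check has a reading of the text and an illustration.

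**Text.** Step 7, the follow-up text and the Drug Chart note all put the chart to every caregiver. None of them says whether the answer is recorded before medicines are looked at, whether the two sources have separate fields, or which source feeds the treatment table. Annex 5, which could settle this, is not yet written.

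**Inputs from the Protocol.** At each site, 200 children with pneumonia are followed up at 2 weeks and 100 at 4 weeks. The important difference is 10 points. Planning values are 60–70% for sensitivity and 70–90% for specificity.

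**Assumed inputs (not in the Protocol).**
- *s*, true accuracy of unaided chart recall: 70%.
- *q*, share of answers taken from an observed pack: 10% to 40%.
- Pack-based answers are always correct and are counted in the chart table.

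**Formula.** Observed accuracy = *q* + (1 − *q*) × *s*. For example, *q* = 0.30 gives 0.30 + 0.70 × 0.70 = 0.79.

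| Pack share, 2 / 4 weeks | Observed if true accuracy is 70% / 70% | Gap (true 0) | Observed if true accuracy is 70% / 60% | Gap (true 10) |
|---|---|---|---|---|
| 10% / 10% | 73% / 73% | 0 | 73% / 64% | 9 |
| 20% / 10% | 76% / 73% | 3 | 76% / 64% | 12 |
| 30% / 10% | 79% / 73% | 6 | 79% / 64% | 15 |
| 40% / 10% | 82% / 73% | 9 | 82% / 64% | 18 |
| 40% / 20% | 82% / 76% | 6 | 82% / 68% | 14 |

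With equal true accuracy, the false gap is (1 − *s*) × (*q* at 2 weeks − *q* at 4 weeks). It is zero when pack shares are equal. Chart accuracy itself is still raised by (1 − *s*) × *q*: 0.30 × 0.10 = 3 points at a 10% share and 0.30 × 0.40 = 12 points at 40%. That excess goes straight into the contrast with DHS/MICS.

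**Setting pack-based answers aside.** Take the 200 and 100 children with pneumonia at one site as the denominators, which assumes that all of them received the drug in question. Pack shares of 20%/10% leave 200 × 0.80 = 160 and 100 × 0.90 = 90. Shares of 40%/10% leave 120 and 90. Power for 70% versus 60% is Φ{[0.10 − 1.96 × √(p̄(1 − p̄)(1/n₁ + 1/n₂))] / √(0.70 × 0.30/n₁ + 0.60 × 0.40/n₂)}, where p̄ is the pooled proportion. The two-sided 5% level is assumed, since the Protocol states none.

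- 200 v 100: 41%
- 160 v 90: 36%
- 120 v 90: 33%

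With the chart answer recorded first for every child, *q* = 0 at both times. The observed gap then equals the true gap and no child is set aside.

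**The case against.** A reader might infer that chart recall is missing wherever packs are kept and that the 2- versus 4-week comparison is biased. The Protocol supports neither statement. The chart is put to every caregiver, no passage exempts homes with packs, and the step 7 wording also fits two recorded answers. Whether any bias arises depends on pack retention, which the Protocol does not give; with equal retention and equal true accuracy the false gap is zero. Step 7 also cannot reach the DHS/MICS treatment answers or the recall of diagnosis, which are taken earlier, or the written records, which are a separate step.

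There is more to say for the plan. The treatment table is worded as the mother's own report. The source note shows that the authors foresaw the two sources and wanted to tell them apart, and flagged answers can be analysed separately. The form is openly unfinished, and forms are finalised only after training and the pilot. Treating packs as always correct is itself generous: the reference is what the clinic prescribed, and a pack at home may come from another source or another episode.

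These points limit the strength and scope of the concern. They do not remove it. Step 7 is a stated data-collection instruction, and none of these passages tells the interviewer to secure the unaided answer first. If that answer is not recorded at the visit, no later analysis can recover it. Analysing flagged children apart costs numbers and may select homes.

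**Conclusion.** The point holds as a gap in the instruction, with a possible and not a demonstrated bias. Step 7 puts chart recall and observed medicines under one source note and fixes neither order nor separate recording. Three results may therefore mix recall with label reading: chart sensitivity and specificity, their contrast with DHS/MICS recall, and the chart-based part only of the 2- versus 4-week comparison.

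On the assumed values, the false gap between recall periods runs from 0 points with equal pack shares to 9 points at 40% versus 10%. Chart accuracy is raised by 3 to 12 points over pack shares of 10% to 40%. All of this rests on assumed retention, 70% true accuracy, packs that are always right, and pack-based answers being counted in the chart table. A stated outcome is exposed and the remedy is cheap, so the change should be made before the home form is completed.

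**What to change.** Split step 7 in two.

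- **7a.** Show the chart to every caregiver, then record and close her answer before any medicine or note is brought out.
- **7b.** Ask to see medicines in the home and record them in a separate field on the Annex 5 form.

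State under Study analysis that the treatment table for the chart method uses only the 7a answer, for every child. Report the 7b medicines, with the step 8 records, as a further source.

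The cost is one line in the interview sequence, one extra field on a form that is still to be written, and one sentence in the analysis text. It needs no more children or staff and does not change the sample size.

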***This same table will be used for the MICS diagnosis**

|  | | **Medical diagnosis of Pneumonia** | | |
| --- | --- | --- | --- | --- |
|  | | **+ve** | **-ve** | **Total** |
| **Does child reach specific pneumonia score (e.g. 5)** | **Y** | **a** | **B** | **a+b** |
| **N** | **c** | **D** | **c+d** |
| **Total** | **a+c** | **b+d** | **n** |

|  | | **Medical diagnosis of Pneumonia** | | |
| --- | --- | --- | --- | --- |
|  | | **+ve** | **-ve** | **Total** |
| **diagnosis of pneumonia**  **from video** | **+ve** | **a** | **B** | **a+b** |
| **-ve** | **c** | **D** | **c+d** |
| **Total** | **a+c** | **b+d** | **n** |

- Sensitivity = a/(a+c)
- Specificity = d/(d+b)

We will use Receiver operating characteristic (ROC) curves to present the results of the pneumonia score to determine the most appropriate score threshold.

We will also assess the validity of the report of treatment received in the same way.

|  | | **Child received drugX*** | | |
| --- | --- | --- | --- | --- |
|  | | **Y** | **N** | **Total** |
| **Mother said child received drugX*** | **Y** | **a** | **B** | **a+b** |
| **N** | **c** | **D** | **c+d** |
| **Total** | **a+c** | **b+d** | **n** |

*Drug X will be substituted for each of the medications listed

**Sample size calculation (see Table 2)**

The sample size calculation was based on two main considerations:

- Sample size to estimate sensitivity and specificity with a precision of +/- 5% based on baseline estimates of sensitivity of 60-70% and specificity of 70-90% (see table). Table 2 suggests that a sample size of 300 cases and 300 controls will achieve this.
- Sample size to distinguish a 10% difference (considered to be a programmatically important difference) in sensitivity and specificity with 80% power between estimates based on 2 week versus 4 week recall. Depending on the baseline level of sensitivity and specificity Table 2 suggests that a sample size of approximately 300 cases and 300 controls will achieve this. Note that a combined analysis across the two sites should have power to detect a smaller difference of the order of +/- 7-8%

Each study will therefore aim to achieve a completed sample size (with successful follow up) of 300 children under age five with physician-confirmed clinical pneumonia, and 300 children confirmed by a physician not to have pneumonia.

**Study organization and management**

**Study Management**

[name] will have overall responsibility for the study. He will be assisted by [name], who will conduct initial visits to each site to finalize the study protocol and ensure data quality and comparability across sites, and a follow-up visit to each site shortly after data collection begins. [name] [name] and [name] will be responsible for managing the day-to-day activities and conducting the primary analysis.

*Site specific preparation before recruitment*

*Ethical approval*

This will be sought from the appropriate authorities at each study sites and WHO Ethics committee. Each site will be responsible for preparing study recruitment, follow up and consent forms in the local language and for obtaining local ethical approval.

*Producing a pneumonia video*

Each site will be required to produce a video (at least 2 minute clip) of at least one child displaying the clinical signs of pneumonia (fast breathing of at least 10 breaths/minute above the threshold for that age and lower chest indrawing ) and at least one child demonstrating signs of “cough or cold” (blocked or runny nose and noisy upper respiratory breathing but NO fast breathing at least 10 breaths /minute below the age threshold) and upload it onto the study PC (or DVD player) with a medium sized screen that will be used for the interviews. There should be a video made of a 2 month old child and a 2 year old child for both pneumonia and “cough and cold”. The pilot test of the video will check that the video quality is appropriate for the study so that poor quality does not give falsely poor results.

*Developing a pneumonia score*

The pilot study will include a check of the face validity and cultural appropriateness of the items in the study protocol together with some formative research to identify local and commonly used terms for some of the items in the list, e.g. restlessness, flared nostrils, irritability etc.

*Identifying and documenting local treatments*

Each study site will also be required to document all drugs which are commonly used in that area to treat pneumonia, malaria and other febrile illnesses. They will also be required to take pictures of the individual pills/syrups/injections, which will then either be loaded onto the study PC, or printed on to a “pill board”.

*Training*

An experienced senior researcher will visit each study site before and once during the study period to ensure study procedures are being followed closely and in a similar fashion at each site. Training of clinic doctors and research worker s who conduct the follow up will cover

- Diagnosis of pneumonia
- Preparation of local pneumonia score and videos
- Study record forms
- MICS or DHS survey procedures
- Pilot study using the study procedures to recruit and follow up children to check that there are no major flaws in the planning or structure of the study and to address any problems which arise (this should include at least 5 children with pneumonia and 5 with “cough or cold”.
- Technical issues related to the video / PCs

This study forms will only be finalised after the training and pilot period and with the active participation of [name], WHO.

Plan of Analysis

The data sets will be used to describe the sensitivity and specificity of reported signs of suspected pneumonia for “proven pneumonia” (a pneumonia score system will give a range of sensitivities and specificities for each score – which will enable a cut off score to be selected with the best sensitivity and specificity) for the current DHS protocol and for alternative protocols using the combinations of the three strategies described above. In addition, the study team will compare the results obtained using two- and four-week recall periods.

Project outcomes:

- Sensitivity + specificity of interview based diagnosis of pneumonia with existing DHS / MICS survey methods; pneumonia score and video-assisted recall.
- Sensitivity + specificity of mothers recall of treatments with existing DHS / MICS survey methods and new pictorial approaches

Comparison of results from 2 weeks and 4 weeks recall period (including a comparison of recalled timing of delay in careseeking at these different time points).

